### Data monitoring body

2.8

An independent data safety monitoring board is in place to monitor the safety of intensive BP lowering as well as repeated CT perfusion studies. The board reviews clinical and imaging data in batches of 10 patients each. Unexplained clinical deterioration in intensive BP control arm is reviewed in a multidisciplinary meeting (neurologists, neurosurgeons, neuroradiologist, and interventional neuroradiologists). Treating stroke neurologist is allowed to discontinue intensive BP lowering treatment (if the subject is allocated to this treatment arm), if this is considered to be the sole/leading cause of neurological deterioration. Radiation safety officer will be using the real patient data as well as a phantom to monitor radiation exposure to brain, eyes, and thyroid gland. For reassurance, we used a phantom and evaluated the radiation dose exposure for one non-contrast CT (NCCT) + CT angiogram + CT perfusion (CTP), which was quite low as 6.13 mSv.

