## Introduction and rationale

1

Elevated systolic blood pressure (BP), defined as >140 mm Hg, is commonly observed in patients with acute ischemic stroke (AIS).^[1]^ Potential mechanisms and associations include pre-existing hypertension,^[1]^ activation of neuroendocrine systems,^[2]^ stress of hospitalization,^[3]^ location of the infarct,^[4]^ stroke subtype,^[5]^ severity,^[6]^ and a homeostatic response to raised intracranial pressure.^[7]^ Whether treatment of this acute hypertensive response improves clinical outcome is unknown.^[7,8]^ Arguments in favor of treatment include the strong positive relationship between degree of elevation in BP and death or dependency,^[9]^ cerebral edema,^[10]^ early and late stroke recurrence,^[11,12]^ and extrapolation of potential benefits in acute intracerebral hemorrhage (ICH).^[13–15]^ Arguments against treatment center on the natural tendency for BP to normalize within a few days of presentation,^[1,5,6]^ and potential harms associated with altered cerebral perfusion related to dysfunction of autoregulation.^[7,16,17]^ Some studies suggest that adverse outcomes are associate with early antihypertensive therapy.^[18,19]^

The primary aim of the study is to determine the effect of early intensive BP lowering (systolic BP target 140–160 mm Hg) initiated within 6 hours of symptom onset and maintained for 72 hours in AIS patients treated with intravenous tissue plasminogen activator (IV-tPA) on cerebral blood flow (CBF), measured with computed tomographic (CT) perfusion imaging. We hypothesize that this treatment approach is safe and that such magnitude of BP lowering does not reduce CBF by 20% and/or increase the volume of hypoperfused tissue by >20% on CT perfusion or adversely affect functional outcomes at 90 days. Secondary aims are to obtain preliminary estimates of the clinical impact of early intensive BP lowering on functional outcomes and symptomatic intracerebral hemorrhage (sICH).

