### Outcomes

2.7

The primary outcome is the assessment of CT perfusion studies and evaluate whether CBF in the affected region reduces by >20% and/or the volume of hypoperfused tissue increases by >20% if BP is treated intensively during the first 72 hours in thrombolysed AIS patents. Secondary endpoint is dependency at day-90, defined by scores 2 to 6 on the mRS. Secondary outcome would be sICH, defined by the Safe Implementation of Thrombolysis in Stroke-Monitoring Study (SITS-MOST) criteria as large local or remote parenchymal ICH (type 2) combined with a neurological deterioration (≥4 points on the NIHSS) from baseline or death within 36 hours.^[20]^ Data are entered prospectively on to case report forms without any personal identifiers.

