### Sample size calculations

2.11

Allowing for within-subject and between-subjects variation, a sample size of 27 patients per group was estimated to allow detection of a difference of 20% [15% standard deviation (SD)] in relative change in CBF and/or the volume of hypoperfused tissue between the early intensive BP lowering and control groups, with 90% power and significance set at 5% (α = 0.050, 2-tailed). The sample size was increased to 30 patients per group to allow for treatment dropouts, crossovers, and potential loss to follow-up.

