### Statistical analysis

2.12

Data will be analyzed blind to treatment group according to the intention-to-treat principle by an independent biostatistician. Continuous variables will be presented as mean (SD) and nominal variables tabulated as absolute and/or relative frequencies. Comparisons between binary outcomes will be performed using Fisher exact test. Continuous variables will be compared using the unpaired *t* test and Mann-Whitney *U* test as indicated. Comparisons of BP and NIHSS scores between the 2 groups at different time-points will be analyzed using repeated-measures analysis of variance for the overall effect. Finally, the relative changes in BP, CBF, and NIHSS scores at 1, 24, and 72 hours after the initiation of treatment, and 90-day outcomes, will be compared using analysis of covariance. Baseline BP and use of antihypertensive medications before admission will be used as covariates in analyses of BP differences. Baseline NIHSS will be used as a covariate in analyses of stroke severity. Statistical significance is set at the 5% level. There would be no interim analysis (Table 3).

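### Intensive lowering may be stopped because of apparent harm, yet later scans still count for that arm, so intention-to-treat can understate the 72-hour effect the trial asks about

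*Protocol article*

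**What the plan says.** All of the following is in the Protocol article.

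- **Question.** The Introduction describes lowering "initiated within 6 hours of symptom onset and maintained for 72 hours" and hypothesises that "such magnitude of BP lowering does not reduce CBF by 20% and/or increase the volume of hypoperfused tissue by >20% on CT perfusion". Section 2.7 (Outcomes) frames the primary outcome as whether CBF in the affected region falls by more than 20% and/or "the volume of hypoperfused tissue increases by >20% if BP is treated intensively during the first 72 hours".
- **Stopping.** Section 2.8 (Data monitoring body): "Treating stroke neurologist is allowed to discontinue intensive BP lowering treatment (if the subject is allocated to this treatment arm"), and the trigger is "if this is considered to be the sole/leading cause of neurological deterioration". Section 2.3 says the treating physician knows the allocation.
- **Scans.** Sections 2.4 and 2.6 schedule CT perfusion at 24 and 72 hours after randomisation for all patients. No exception is made for those who stop, and no scan is tied to stopping.
- **Analysis.** Section 2.12: "Data will be analyzed blind to treatment group according to the intention-to-treat principle by an independent biostatistician". No other analysis set is named.
- **Allowance.** Section 2.11: "The sample size was increased to 30 patients per group to allow for treatment dropouts, crossovers, and potential loss to follow-up". The increase is from 27, so 3 patients per group.

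**The concern.** Stopping is stated for one arm, is decided by someone who knows the allocation, and is triggered by the kind of harm the hypothesis denies. A patient whose perfusion falls under intensive lowering, who deteriorates and is then stopped, may be scanned after BP has risen and flow has recovered. Under intention-to-treat that scan is an intensive-arm value. In a trial that looks for a difference such dilution is conservative. Here the hoped-for conclusion is that worsening stays within 20%, so dilution favours it.

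The 3 extra patients per group protect the number analysed. They do not move the diluted average back.

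At stake is whether preserved CBF in the report would mean that 72 hours of lowering is tolerated, or partly that treatment was withdrawn from patients who did not tolerate it.

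**Working it through.** **Inputs from the plan (section 2.11):** difference 20%, SD 15%, 90% power, two-sided 5%, 27 per group.

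**Assumed, because the plan gives no figure:** the share *p* of the intensive arm who stop before the scan, and how far perfusion recovers by then.

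**1. The plan's own figure.** n = 2(1.960 + 1.282)² × 15² / 20² = 11.8, so 12 per group (13 with the t distribution), not 27. Working back, 27 per group implies an SD of 20/(1.960 + 1.282) × √(27/2) = 22.7. The plan says it allowed for within- and between-subject variation but gives no components. That is a separate matter; it matters here only because both SDs are therefore carried forward.

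**2. Size of the dilution.** Count worsening as positive. Let the sustained effect sit exactly at the margin, with individual worsening N(20, SD) and a control mean of 0.

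- If those who stop are a random subset and return to the control mean, the intention-to-treat difference is 20(1 − p).
- If they are the worst affected, it is 20 − [20p + SD × φ(z)], where φ is the normal density and z the upper-*p* point.

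For p = 0.10 and SD 15, φ(z) = 0.1755, which gives 20 − (2.0 + 2.63) = 15.4.

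The chance of wrongly concluding less than 20% worse is Φ[(20 − difference)/SE − 1.96], with SE = SD√(2/27). This takes the conclusion to require a 95% upper limit below 20%.

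| p | Who stops | Difference, SD 15 | False no-harm, SD 15 | Difference, SD 22.7 | False no-harm, SD 22.7 |
|---|---|---|---|---|---|
| 0 | – | 20.0 | 2.5% | 20.0 | 2.5% |
| 5% | random | 19.0 | 4.3% | 19.0 | 3.6% |
| 5% | worst | 17.5 | 9.1% | 16.7 | 7.8% |
| 10% | random | 18.0 | 7.1% | 18.0 | 5.1% |
| 10% | worst | 15.4 | 20.5% | 14.0 | 16.1% |
| 20% | random | 16.0 | 16.4% | 16.0 | 9.5% |
| 20% | worst | 11.8 | 51.9% | 9.7 | 38.9% |

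**3. Partial recovery (SD 15).** The worst 10% average 46.3 and the worst 20% average 41.0. If they recover halfway, the arm mean is 20 − 0.10 × 46.3/2 = 17.7, or 20 − 0.20 × 41.0/2 = 15.9.

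The share of patients beyond 20% starts at 50%. With full recovery it falls to 40% or 30%. With half recovery a stopped patient still exceeds 20% if the original fall was above 40%, which has probability 9.1%. The share is then 50 − 10 + 9.1, about 49%, or 50 − 20 + 9.1, about 39%. At 10% stopping the threshold count barely moves.

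**4. The test actually planned.** Section 2.11 describes a two-sided difference test. With the worst 10% stopped and fully recovered, power falls from 99.8% to 96% (SD 15), or from 90% to 62% (SD 22.7). The risk in that setting is that a non-significant result is read as safe.

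**5. Would an on-strategy analysis cure it?** Not alone. Dropping the worst 10% gives a mean of about 17.1 (SD 15), closer to 20 than the 15.4 under intention-to-treat but still diluted. In simulation (27 per group, SD 15, worst 10% stopped, full recovery) the false no-harm rate is about 22% under intention-to-treat, and 11% if both analyses must agree. With half recovery the agreement requirement adds almost nothing (8.5% to 8.4%).

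**The case against.** The strongest reply is that intention-to-treat is the right principle and is unbiased for the strategy as it would be used, safety stop included. The hypothesis that the approach is safe can be read that way. Intention-to-treat also keeps the harmed patients in their arm. This stands: the understatement exists only relative to sustained lowering. But the Introduction and section 2.7 describe treatment maintained over 72 hours, so the plan has to say which question it means.

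Second, several things must coincide: stopping before a scan, stopping related to low perfusion, and recovery before that scan. A 24-hour scan taken before stopping, or irreversible injury, still shows the harm. The trigger is clinical and narrow and does not rank patients by CBF, so the worst-affected rows are an upper-limit scenario. All of this stands.

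Third, harm is watched elsewhere: NIHSS is recorded daily and compared between arms, 90-day mRS is a secondary endpoint, and a board reviews data every 10 patients. True, but none of this enters the primary perfusion outcome.

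Fourth, the full protocol or a statistical analysis plan may already deal with early stopping. The article shows only that question and named analysis do not match, not that no supplementary analysis exists.

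Fifth, scoring every stop as harm in the primary outcome would bring an unblinded, one-arm judgement into a blinded, centrally read imaging measure. That is a fair objection, and the reason to confine such scoring to a sensitivity analysis.

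A reader might infer that the no-harm conclusion is biased, or that intention-to-treat should be replaced. The documents support neither: no stopping rate or recovery is documented, and excluding those who stop also leans towards no harm.

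**Conclusion.** The point holds in conditional form. The article poses its no-harm question about lowering sustained for 72 hours, permits outcome-driven stopping that it states for the intensive arm only, and names only an analysis that can understate the sustained effect when stopping comes before a scan and perfusion recovers. The direction, where there is any effect, is towards no harm.

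The size cannot be derived from the documents. If 10% stop and recover fully, a true 20% worsening would appear as about 14% to 18%, and a nominal 2.5% false no-harm rate would become about 5% to 20%, depending on who stops and on the SD. These figures assume normal responses, 27 per group and a margin-type conclusion that the article does not formally specify. With partial recovery the effect is smaller; with no stopping or no recovery it is zero.

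**What to change.** - State whether the primary question concerns the strategy including permitted stopping, or lowering sustained for 72 hours.
- Keep intention-to-treat as the primary analysis.
- Record the time and reason of every departure from the allocated strategy, in both arms.
- Prespecify, before unblinding, two supporting analyses: (a) a sensitivity analysis in which a patient whose allocated strategy is stopped for neurological deterioration before 72 hours counts as meeting the 20% harm criterion, with the worst rank for continuous measures; and (b) an analysis of scans taken while on the allocated strategy, with a note that (b) alone is also diluted.
- Claim no worsening beyond 20% only if both agree with intention-to-treat.

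The cost is some analysis wording, one case report form field and one or two extra analyses, with no added scans or patients. The result may be slightly less favourable to the intensive arm, because (a) counts some patients as harmed whatever their scan shows. The clinical stopping decision is unchanged.

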### CT perfusion acquisition

2.9

With dynamic, quantitative CT perfusion, an additional contrast bolus of 35 to 45 mL is administered via an injector (at a rate of 7 mL/s), with a saline “chaser” of 20 to 40 mL at the same injection rate. The contrast used (omnipaque) has high concentration, typically 350 to 370 g/dL for optimal signal-to-noise ratio for perfusion maps calculation. Imaging begins a few seconds after injection, and selective axial sections to image selected areas of the brain using “toggle mode” expands the anatomic coverage by toggling the table between 2 locations during dynamic scanning of 4 cm cuts of the brain. A Philips 64 slice scanner with standard resolution is used with collimation 32 × 1.25, thickness 5 mm, 3.8 seconds cycle time, 80 kV at 150 mA, matrix 512, and window-center/width of 40/80. Scans take 55 to 60 seconds to complete 15 jog cycles.

### CT perfusion image analysis

2.10

Perfusion images will be analyzed centrally by investigators blinded to BP treatment and clinical data. Raw CTP source images will be transferred to a computer workstation and postprocessed using the MIStar software package, version 3.2 (Apollo Medical Imaging Technology, Melbourne, Australia). An arterial input function will be selected automatically in the contralateral middle cerebral artery. An arrival time insensitive singular value decomposition, deconvolution algorithm will be used to calculate voxel-wise maps of CBF, cerebral blood volume (CBV), mean transit time (MTT), and delay time to peak of the residual function (DT).^[16]^ The total perfusion deficit volume will defined using a threshold DT >6 seconds (DT). The pretreatment (baseline) ischemic core will be defined as tissue with a CBF of <30% inside the perfusion deficit. The penumbra will be defined as tissue within the DT deficit which was not the ischemic core [i.e., relative CBF (rCBF) >30%]. Hypoperfused tissue, penumbral, and core volumes will be measured at all 3 time points.^[17]^

Final infarct regions of interest will be drawn on the 24 hour NCCT and coregistered to CBF, CBV, MTT, and DT maps obtained at all 3 time points. The mean absolute perfusion value within each region will then be measured. Mean perfusion values will also be measured in homologous regions of the contralateral hemisphere. rCBF, relative CBV, and relative MTT will be calculated as the ratio of the absolute mean value in the infarct core and homologous contralateral region. Relative DT will be defined as the difference between the absolute mean in infarct region and that in the contralateral homologous region.

### Sample size calculations

2.11

Allowing for within-subject and between-subjects variation, a sample size of 27 patients per group was estimated to allow detection of a difference of 20% [15% standard deviation (SD)] in relative change in CBF and/or the volume of hypoperfused tissue between the early intensive BP lowering and control groups, with 90% power and significance set at 5% (α = 0.050, 2-tailed). The sample size was increased to 30 patients per group to allow for treatment dropouts, crossovers, and potential loss to follow-up.

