**Methods::**

In a randomized controlled trial, 54 thrombolysed AIS patients with a systolic BP of 160 to 180 mm Hg will be randomized to early intensive BP lowering (systolic target range 140–160 mm Hg) or guideline-based BP management (systolic range 160–180 mm Hg) during first 72-hours using primarily intravenous labetalol. We hypothesize that early intensive BP lowering will not reduce CBF by 20% and/or increase the volume of hypoperfused tissue by >20% on computed tomographic perfusion. Clinical outcome will be assessed using a dichotomized modified Rankin scale (scores 0–1 as excellent outcome vs scores 2–6 as dead or dependent) at 90 days. Other outcome would be symptomatic intracerebral hemorrhage. The trial is registered at ClinicalTrials.gov, NCT03443596.

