### Randomization and blinding

2.3

All study subjects undergo CT perfusion to obtain the baseline cerebral hemodynamic parameters. Participating patients are randomly assigned to early intensive BP lowering (140–160 mm Hg) or the guideline-based management (160–180 mm Hg) in a 1:1 ratio using a central computer generated sequence with minimization according to age (<60 vs ≥60 years), severity (NIHSS score <10 vs >10), and baseline systolic B (<150 vs >150 mm Hg). The treating physician is unblinded to the treatment assignment as he/she is required to titrate BP control with IV labetalol. However, all 90-day outcome assessments are conducted by physicians who are kept blind to the treatment allocation.

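### The 27 per group in section 2.11 does not follow from its printed inputs, which need about 13, and the number to be randomized is given as both 54 and 60

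*Protocol article*

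**What the plan says.** Section 2.11 (Sample size calculations) states that "a sample size of 27 patients per group was estimated to allow detection of a difference of 20% [15% standard deviation (SD"). The measure is the relative change in CBF, in hypoperfused volume, or in both, compared between the two groups, "with 90% power and significance set at 5% (α = 0.050, 2-tailed"). The sentence opens with a qualifier, "Allowing for within-subject and between-subjects variation", but gives no variance component, correlation or design factor.

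The section then adds a margin: "The sample size was increased to 30 patients per group to allow for treatment dropouts, crossovers, and potential loss to follow-up". Two groups of 30 make 60. No loss rate is given.

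The Methods paragraph of the abstract gives a different total: "54 thrombolysed AIS patients with a systolic BP of 160 to 180 mm Hg will be randomized to early intensive BP lowering". That is 2 × 27, the figure before the margin.

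Section 2.3 sets allocation "in a 1:1 ratio using a central computer generated sequence with minimization". Section 2.12 compares continuous variables by the unpaired t test or the Mann-Whitney test, and relative changes in CBF by analysis of covariance.

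**The concern.** A 20-point difference with an SD of 15 points is a standardized difference of 1.33, which is very large. Such an effect needs roughly a dozen patients per group for 90% power, so 27 is about twice what the printed inputs call for. The gap is too large to come from rounding or from the choice between a normal and a t calculation.

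The SD matters here because the main hypothesis is one of safety: that intensive lowering does not reduce CBF by 20% or enlarge the hypoperfused volume by more than 20%. How far a result near zero reassures depends on its precision, and precision depends on the SD. A reader cannot tell whether to expect the precision of an SD of 15% or of about 22%.

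The two totals raise a second question. If recruitment stops at 54, the whole margin for dropouts, crossovers and loss to follow-up is gone. The article does not say which number governs.

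**Working it through.** **Inputs.** From section 2.11: difference Δ = 20 points, SD σ = 15 points (read as the SD of the relative change, as the sentence has it), power 90%, two-sided α = 0.05. From section 2.3: 1:1 allocation. From section 2.12: unpaired t test.

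**1. The printed inputs.** Normal approximation, per group:

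n = 2 (z₀.₉₇₅ + z₀.₉₀)² (σ/Δ)² = 2 × (1.960 + 1.2816)² × (15/20)² = 2 × 10.51 × 0.5625 = 11.8, so 12.

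The exact (noncentral t) solution is 12.86, so 13 per group and 26 in all. The stated 27 is not reproduced.

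**2. Power of the stated size at the printed inputs** (t test): 99.8% with 27 per group and 99.9% with 30 per group, against the stated 90%.

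**3. What 27 per group implies.** The t test with 27 per group and 90% power detects a standardized difference of 0.899. Then:
- with Δ = 20, the SD is 20/0.899 = 22.2 points;
- with SD = 15, the detectable difference is 0.899 × 15 = 13.5 points.

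Neither figure is in the text.

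**4. Whether the variance qualifier closes the gap.** Suppose that 15% is the SD at a single scan and that ρ is the correlation between two scans of one patient. The SD of the change is then 15 × √(2(1 − ρ)).

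| ρ (assumed) | SD of change | n per group, t test |
|---|---|---|
| 0 | 21.2 | 24.6, so 25 |
| 0.25 | 18.4 | 18.7, so 19 |
| 0.5 | 15.0 | 12.9, so 13 |

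Adding a within-subject and a between-subject component of 15% each gives the same 21.2 and 25. So the most favourable simple reading, with uncorrelated scans in the same patient, ends two short of 27; at that SD, 27 per group has 92.5% power.

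**5. Other single changes to the design** (per group, SD 15%): one-sided test, 10 to 11; Mann-Whitney efficiency correction, 14 to 15; α split over the two perfusion measures, 14 to 16; that split with 90% joint power, 17 to 19; non-inferiority with a true difference of zero, 12; two one-sided equivalence tests, 13 to 15. None gives 27.

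**6. The margin and the totals.** 27/0.9 = 30, so the increase matches a 10% loss; that rate is my inference. The totals are 2 × 27 = 54 (abstract) and 2 × 30 = 60 (section 2.11).

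**7. What the choice of total does to power.** With 10% loss from 54, 27 × 0.9 = 24.3 per group remain.
- SD 15%: power is 99.5% with 24 per group, so the choice hardly matters.
- SD 22.2%: power is 86 to 87% with 24.3 per group, against 90% with the 27 per group left after the same loss from 60.

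**The case against.** The strongest reply is that the sentence does not claim to be a bare two-sample calculation with SD 15%. It says that within- and between-subject variation was allowed for, and a condensed article may leave the components to the full protocol. Read as a per-scan SD with uncorrelated scans, 15% already leads to 25. Combined assumptions can even reach 27: a between-scan correlation of 0.1 gives an SD of 20.1, and with α = 0.025 for each of two measures the t test needs 26.4, so 27.

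Part of this stands. A reader might infer that the stated power and the stated size are both wrong, and the article does not support that. If the planners used an SD near 22%, then 27 per group and 90% power agree, and only the printed SD misleads. The reply does not rescue the sentence as printed, however. Its wording attaches 15% to the relative change, its α is 0.050 and not 0.025, and it prints no correlation.

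Two other inferences should be resisted. One is that 27 is a two-group total reported as a per-group number: the t-test total is 26, and the abstract's 54 fits 27 being meant per group. The other is that the trial is too small: at the printed inputs either total leaves power above 99%. Nor does a surplus over 13 per group show that patients are scanned needlessly, since the article also seeks preliminary estimates of functional outcome and of symptomatic haemorrhage.

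None of this touches the conflict between 54 and 60. Both are current statements in the same article.

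**Conclusion.** The calculation does not follow from its printed inputs. They need about 13 per group, and with 27 per group they give 99.8% power, not 90%. At least one of the SD, power and n is therefore wrong or is not the figure used; an SD of about 22%, or a difference of about 13.5 points, would make the rest consistent. The article does not show which. This rests on a two-group comparison of mean relative change with the SD taken as worded.

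The number to be randomized is contradictory, 54 against 60, and this needs no assumption. Its consequence depends on the first point: negligible at SD 15%, and a fall to about 86 to 87% power if the SD is about 22%, recruitment stops at 54 and loss is about 10%. Underpowering is thus conditional on an SD that the article does not state.

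**What to change.** In section 2.11, do one of two things:
- state the SD actually used (about 22% if 27 per group and 90% power are meant), what it refers to (a single scan or the relative change), and the within-patient correlation assumed; or
- keep the SD of 15% for the relative change, and state that 27 per group gives 99.8% power for 20 points, or 90% power for about 13.5 points.

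Then give one randomized total in both the abstract and section 2.11. If that total is 60, say that 54 is the number expected to be analysable, and state the loss rate assumed. If it is 54, delete the increase to 30 per group and give the power after expected loss.

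This costs a few sentences. It requires no change in enrolment, procedures or analysis.

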## Discussion

3

As a U-shaped relationship of systolic BP and outcomes after IV-tPA is suggested in various studies,^[8,10,12]^ both high and low systolic BP are considered harmful. Interestingly, the nadir for optimal outcome appears to be a systolic BP of 140 to 160 mm Hg. Thus, we hypothesize this systolic BP as being the best target for functional outcome and reduced risk of sICH.

Labetalol was chosen for BP lowering because of ready availability, minimal adverse effects on heart rate, and cardiac output due to being a mixed α and β antagonist effects, rapid onset of action (5 minutes) and reasonable duration of action (3–6 hours). Studies indicate stable effects of labetalol on CBF, cerebral oxygen consumption, and cerebral circulation.^[21,22]^ There is good experience of the use of labetalol in patients with AIS^[23]^ and it has a predictable and uniform dose-response relationship.^[23]^

With serial BP measurements (including comparison of different intensities of BP lowering), NIHSS and repeated CT perfusions, this study will provide mechanistic data to elucidate the relationship between BP, cerebral perfusion, and functional outcomes in thrombolysed AIS cases. Our findings may assist the ongoing studies (such as ENCHANTED BP intensity arm results due in early 2019) and improve the design of future clinical trials of BP management in AIS (in thrombolysed and endovascularly treated) patients.

Finally, we wish to clarify that study is not aimed at evaluating the relationship between early intensive BP reduction and arterial recanalization or persisting occlusion. Study participants are recruited after the arterial recanalization treatment strategies (IV thrombolysis and/or EVT) have already been implemented. While the first CT perfusion serves as the baseline for a particular patient, subsequent perfusion scans provide information about the longitudinal changes in cerebral hemodynamic parameters in response to the changes in BP levels.

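### The 20% limit in the hypothesis has no stated reference, and the trial is sized on a different quantity that matches it against control only if controls stay at baseline

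*Protocol article*

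**What the plan says.** The Abstract, the Introduction and section 2.7 all express the perfusion question as a 20% limit. Section 2.7 asks whether "CBF in the affected region reduces by >20% and/or the volume of hypoperfused tissue increases by >20% if BP is treated intensively". None of the three says whether the change is measured from the patient's own first scan or against the control arm.

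Section 2.11 uses another quantity. The trial is to allow "detection of a difference of 20% [15% standard deviation (SD)] in relative change in CBF and/or the volume of hypoperfused tissue", and the contrast is "between the early intensive BP lowering and control groups". One effect and one SD serve both CBF and volume.

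Section 2.12 compares by ANCOVA "the relative changes in BP, CBF, and NIHSS scores at 1, 24, and 72 hours after the initiation of treatment", together with 90-day outcomes. Hypoperfused volume is not in that list, no 20% limit is applied, and baseline covariates are named only for BP and stroke severity.

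The Discussion makes the first CT perfusion scan each patient's baseline and adds: "Study participants are recruited after the arterial recanalization treatment strategies (IV thrombolysis and/or EVT) have already been implemented".

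**The concern.** The same figure, 20%, stands for a limit on an effect in 2.7 and for a between-arm gap in relative change in 2.11. These agree only under a condition that the article never states. Patients enter after recanalization treatment and are scanned again at 24 and 72 hours, so perfusion may well change in both arms for reasons unrelated to BP. A between-arm gap of 20 points of baseline then no longer means a 20% effect against control, and its meaning differs between volume and CBF.

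At stake is how the primary result is read. Without a named reference, the same data could be described as inside or outside the limit. The stated 90% power also belongs to the quantity in 2.11, which need not be the quantity in the hypothesis.

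**Working it through.** **Inputs from section 2.11.** Difference 20, SD 15, 90% power, two-sided 5%, 27 per group before the allowance for losses.

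**The plan's own figure.** n per group = 2 × (1.960 + 1.282)² × (15/20)² = 11.8, so 12; the t test gives 13. The stated 27 is not reproduced. It would need a total SD of about 22.2 (t test) to 22.7 (normal approximation). That is a separate matter, but it leaves the working SD uncertain, so results are shown for SD 15 and SD 22.2.

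**Assumptions.** Relative change is read as percent change from own baseline. Let c be the control arm's mean ratio of follow-up to baseline. The documents give no value for c, so a range is used. The SD is held constant over c.

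**Conversions.**
- A 20% effect against control is a gap of 20 × c points.
- A 20-point gap is 20/c percent of the control level.
- If the limit is measured from own baseline, the gap needed to reach it is 120 − 100c points for volume and 100c − 80 points for CBF.

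**Volume, 27 per arm.** Power ≈ Φ(20c/SE − 1.96), with SE = SD × √(2/27), which is 4.08 at SD 15 and 6.04 at SD 22.2.

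| c | 20 points as excess over control | 20% excess over control, points | Power, SD 15 | Power, SD 22.2 | n per arm for 90%, SD 15 | Gap to reach +20% from own baseline, points |
|---|---|---|---|---|---|---|
| 1.0 | 20% | 20 | 99.8% | 91% | 12 | 20 |
| 0.8 | 25% | 16 | 97.5% | 75% | 19 | 40 |
| 0.6 | 33% | 12 | 83.6% | 51% | 33 | 60 |
| 0.4 | 50% | 8 | 50.0% | 26% | 74 | 80 |
| 0.2 | 100% | 4 | 16.4% | 10% | 296 | 100 |

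Example at c = 0.4, SD 15: 8/4.08 − 1.96 = 0.00, so power is 50%.

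**CBF.**

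| c | 20 points as deficit against control | 20% deficit against control, points | Gap to reach −20% from own baseline, points |
|---|---|---|---|
| 1.0 | 20% | 20 | 20 |
| 1.2 | 16.7% | 24 | 40 |
| 1.5 | 13.3% | 30 | 70 |
| 2.0 | 10% | 40 | 120 |

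**Reading the tables.** All readings coincide at c = 1 and separate elsewhere. With reperfusing controls and a control-arm reference, 20 points is lax for volume and strict for CBF. With an own-baseline reference, it is strict for both: at c = 0.4 for volume and c = 1.5 for CBF, a 20-point gap puts the intensive arm at −40% volume and +30% CBF, and neither breaches the limit.

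**The case against.** A reader might infer that the plan is simply too lax for volume and too strict for CBF, and would wrongly clear a harmful volume increase. The documents do not support that, for four reasons.

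- **Reference.** The direction needs a control-arm reference. Section 2.7 names none, and the Discussion's account of longitudinal change from the first scan makes an own-baseline reading natural. That reading reverses the direction for volume. On the other side, the Introduction asks for the effect of treatment in a randomized trial, 2.11 contrasts the arms, and a within-arm limit would mix reperfusion with the BP effect. The control-arm reading is therefore the better choice, but it is not the written one.
- **Decision rule.** Section 2.12 applies no 20-point limit, and in 2.11 the 20% is a detectable difference for a two-tailed test. If harm were excluded whenever the upper 95% limit fell below 20 points, a true 20% volume excess over control would pass 49% of the time at c = 0.6 and 82% at c = 0.4 (27 per arm, SD 15). That rule is not in the plan, so these rates only illustrate.
- **Control course.** The baseline scan follows thrombolysis and/or thrombectomy, so part of the reperfusion may precede it, which pulls c toward 1. Section 2.10 measures CBF in the final infarct region, and nothing says that it rises there in controls.
- **Meaning of relative.** Section 2.10 also uses relative CBF for the ratio to the contralateral side. Percent change from baseline is the likely meaning in 2.11 but is not stated.

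Model detail may also sit in an analysis plan that is not shown. All of this stands. It does not remove the gap between 2.7 and 2.11, both of which are fixed in the article.

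**Conclusion.** The point holds as a mismatch of quantities. The hypothesis states a 20% limit without a reference, and the sample size uses a 20% between-arm difference in relative change. They agree as an effect against control only if controls on average stay at baseline, which the article neither states nor supports.

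The size depends on an unknown control course. Over c from 0.8 to 0.4, a 20-point volume gap is a 25% to 50% excess over control. Power for a true 20% volume excess over control at SD 15 stays above 90% at c = 0.8, then falls to about 84% at c = 0.6 and 50% at c = 0.4. It is lower at the SD that 27 per group implies, and the loss would be smaller if the SD shrank along with the volumes. The direction of the mismatch cannot be asserted until the reference is named. Nothing here shows that the written plan would declare a harmful effect safe.

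**What to change.** - **Section 2.7.** State that the 20% limit is the intensive-versus-control effect. For volume, state whether the 20% is of the control level or of baseline, and do not treat the 20-point figure as equivalent to either without saying so.
- **Section 2.12, CBF.** Replace the comparison of relative change with ANCOVA on log follow-up CBF adjusted for log baseline CBF. Report the intensive/control ratio with its 95% confidence interval and read it against 0.80. This answers the question on a proportional scale and can gain precision. In a simulation with assumed log SD 0.25, true ratio 0.80 and 27 per arm, power rose from 77% to 92% at baseline correlation 0.3, and from 89% to 96% at 0.5, compared with an unadjusted t test on percent change.
- **Section 2.12, volume.** Name it as an outcome and compare follow-up volume between arms, adjusted for baseline volume, with a model that accepts zeros.
- **Section 2.11.** Give effect and SD separately for CBF and volume on the chosen scale, and restate the power.

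The wording and the CBF model need no new patients or scans. The cost falls on volume: with a limit relative to control, the stated 90% power may not hold. At SD 15, keeping it would take 33 per arm at c = 0.6 and 74 at c = 0.4. The sponsor should either accept and report the lower precision or justify a volume limit in points of baseline. Percent changes can remain as a descriptive result.
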